### Safety and adverse events

Adverse events (AEs) are undesirable effects that happen to participants during the trial, whether or not they are considered to be related to the infusion system used (standard or Multiline NEO). All AEs during the study must be recorded on the CRF, including the nature of each event, time and date of onset, duration, intensity, criteria of gravity, assessment of cause, need for specific therapy, actions taken, and outcome. According to the severity of AEs, the investigator will determine whether the participant should be withdrawn from the study and which follow-up procedures should be performed. Again these will be recorded in detail. The relationship between the infusion system used and AEs should be assessed and recorded by the investigator.

A serious AE (SAE) is defined as any untoward occurrence or effect that causes death, is life-threatening, requires prolonged hospitalization, results in persistent significant disability, or leads to a congenital anomaly or birth defect. If an SAE occurs, the investigator must immediately report it to the principal investigator and the ethics committee and record it on the CRF with signature and date. A classification of the severity of AEs and their relationship to the infusion system under study is to be established.

An independent supervisory committee will be created. The committee will include a pediatric reanimator, a methodologist, and a pharmacist specialized in medical device vigilance.

### Data collection and management

All data will be recorded by trained clinical investigators in a standardized CRF. To ensure the accuracy and reliability of the data, the study monitor will verify and cross-check the CRFs against the investigator’s source document records. In case of any discrepancies in the cross-checking procedure, the results will be sent to the investigator for resolution. Any individual identification of the subjects will not be released until the database is closed.

Costs related to infusion (medical devices, nursing time) will be estimated by direct observation of micro-costing. Medical devices will be priced according to the invoices paid by the hospitals participating in the study. Actual wages will be taken into account to monetize nursing time. Hospital costs will be estimated from the French DRG database (ENCC). Average costs will be adjusted according to the time spent in NICUs.

### Statistical analysis

Data will be analyzed using SAS software (SAS Institute Inc., Cary, NC, USA) and all statistical tests will be performed with a two-tailed alpha risk factor of 0.05. Baseline characteristics will be described for each group. Quantitative variables will be expressed as mean (standard deviation), median (interquartile range), and range. Qualitative variables will be expressed as frequencies and percentages. Normality of distribution will be assessed graphically and using the Shapiro-Wilk test.

#### Primary outcome

The ID of CRB, expressed as the number of cases of CRB per catheter × days, will be estimated and compared for each of the two devices. The generalized linear mixed model (GLMM) will be used with the number of CRB incidents as dependent variable. The GLMM model will be parametrized with a log linear link function, a Poisson distribution, and the logarithm of catheter duration as the offset variable. To take into account the cluster crossover design, we will consider the device (standard infusion system or Edelvaiss® Multiline NEO), the period, and the ICU as fixed effects and the ICU × interaction period as a random effect as recommended by Turner et al. [19]. Effect size will be estimated by relative risk reduction with a 95% confidence interval.

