Administration of injectable drugs to premature newborn infants presents numerous difficulties, for example, the need for multi-infusion intravenous (IV) therapies and very low infusion rates, limited vascular access sites, and the need to secure the immediate environment around the newborn (elevated temperature and humidity, phototherapy). Catheter manipulations are identified as an essential risk factor for CRB. To this end, Mahieu et al. [6] conducted a study in an NICU on the relationship between infusion line manipulation and CRB. The number of manipulations per catheter ranged from 30.7 up to 300, varying between 0 and 15 per day during the catheterization period. This number of manipulations was significantly different between patients with and without CRB (70.7 vs 28.7, *p* < 0.001) and increased significantly with decreased birth weight. The authors of this work show that some manipulations as well as CVC disconnections increase the risk of CRB. Several types of infusion incidents have been reported, such as hemodynamic instability in infants receiving catecholamines, excessive blood-glucose fluctuations associated with insulin infusion, CRB, and occlusion of the infusion line, to mention a few [7, 8]. According to Kalikstad et al. [9], only 4% of coadministered drugs in NICUs demonstrate unrestricted compatibility. The co-administration of incompatible drugs can have serious consequences for the patient, as drugs may not be totally administered and such incidents require manipulation of infusion lines. Septimus et al. have described several strategies to reduce CRBs, such as minimizing superfluous line manipulations [10]. Preventing particle infusion resulting from drug incompatibilities was found to reduce morbidity and mortality and the length of stay in pediatric intensive care units [11].

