### Sample size estimation

To meet the main objective, we will compare the incidence density (ID) of CRB in the two groups (Multiline NEO and standard infusion system). Determination of the initial risk level is based on data for patients under 29 weeks’ gestational age following the criteria of the Néocat network. With the standard infusion system, the CRB rate is estimated at 18.5 per 1000 catheter-days for this population. It is estimated that the Multiline NEO, correctly implemented, should reduce this rate by 50%. The average duration of catheterization is estimated at 21 days in very low-birth-weight infants. As regards the 50% reduction in CRB rate, there are even more optimistic results to be found in the literature with strategies based on structured methods to improve the care process (bundles and checklists). Erdai et al. [16] showed a 77% reduction in the rate of catheter-related infection with the use of such strategies.

As a result, with a combination of the Edelvaiss® Multiline NEO device and a training program before use, we can assert that the assumption of a 50% decrease in CRB is realistic.

Using a chi-square test at 5% significance level, with 80% power, 2510 catheter-days are required for each group. Given an average duration of 21 days of catheterization, it is therefore necessary to recruit 120 subjects per group (per drug infusion system) without clustering correction. To include clustering effects, we will use the method proposed by Giraudeau et al. [17], estimating the intra-class correlation coefficient (ICC) at 0.01 based on a previous cluster-randomized study in an ICU [18] and the inter-period correlation coefficient at 0.005 (half of ICC as recommended by Giraudeau et al. [17]). This yields 35 as the required number of subjects for each ICU and each period (design effect of 1.16). We therefore plan to recruit a total of 280 patients (140 per group).

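### The Poisson model for CRB counts allows no infant-level dispersion and leans on a 2-df ICU × period term, so the interval for the device effect can be too narrow

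*Protocol article*

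**What the plan says.** Protocol article, Statistical analysis, Primary outcome: the number of CRBs is the dependent variable in a GLMM. "The GLMM model will be parametrized with a log linear link function, a Poisson distribution, and the logarithm of catheter duration as the offset". Device, period and ICU are fixed; ICU × period is the only random term. No infant-level random effect, dispersion scale or robust variance is named, and neither is the estimation method or the denominator df. Occlusions are analysed by the same method (Secondary outcomes). That section gives a fallback for the duration outcomes if residuals are not normal; the count model has none.

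The Abstract says that CRBs and catheters are totalled for each patient. The analysis section does not state the row unit, so infant-level data are inferred. Study design provides for catheter changes, and Study procedure records a number of CRBs at Visit 2, so repeat events are possible. The Discussion says that CRB incidence rises as birth weight and gestational age fall; neither is a covariate in the model.

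Sample size estimation: "the CRB rate is estimated at 18.5 per 1000 catheter-days for this population", a halving is assumed, "The average duration of catheterization is estimated at 21 days in very low-birth-weight infants", and "with 80% power, 2510 catheter-days are required for each group". Then: "Given an average duration of 21 days of catheterization, it is therefore necessary to recruit 120 subjects per group". That sentence goes on to say that the figure precedes any clustering correction; the correction follows, with ICC 0.01, inter-period correlation 0.005 and design effect 1.16.

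**The concern.** If infants differ in underlying risk and can have more than one CRB, the count per infant varies more than a Poisson count. The stated model cannot see this directly. With no infant-level covariate other than the offset, its likelihood depends only on the CRB totals and catheter-days of the eight ICU-periods. Extra variation between infants can enter only as extra variation between ICU-periods, and that is judged on 2 df. Where that variance is estimated at zero, the standard error falls back to the pure Poisson value. At stake is the error rate of the primary test, for which the plan says "all statistical tests will be performed with a two-tailed alpha risk factor of 0.05".

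**Working it through.** **1. The plan's own figure.** With p1 = 0.0185, p2 = 0.00925, mean 0.013875, two-sided alpha 0.05 and power 80%:

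n = [1.960 × √(2 × 0.013875 × 0.986125) + 0.8416 × √(0.0185 × 0.9815 + 0.00925 × 0.99075)]² / 0.00925² ≈ 2509.1, rounded up to 2510 catheter-days. This agrees.

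2510 / 21 = 119.5, so 120 infants. Design effect = 1 + 34 × 0.01 − 35 × 0.005 = 1.165. 120 × 1.165 = 139.8, so 140 per group, 35 per ICU-period and 280 in all. This agrees too. ICU clustering is covered. Dividing catheter-days by 21 treats days within an infant as independent.

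**2. Degrees of freedom.** There are 4 ICUs × 2 periods = 8 cells. The fixed effects have rank 4 + 1 + 1 = 6, which leaves 2 df for ICU × period. Within cells, 280 − 8 = 272 df are unused.

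**3. Size of the inflation.** Expected CRBs per infant: 0.0185 × 21 = 0.3885 on the standard system and 0.19425 at rate ratio 0.5. Let infants differ by a gamma factor of mean 1 and variance θ. **θ is an assumption; the documents give no value.** Then variance/mean = 1 + θ × 0.3885 under the null. At rate ratio 0.5 the variance of the log rate ratio is inflated by 1 + 2θ / (1/0.3885 + 1/0.19425) = 1 + 0.259θ.

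| θ | Variance/mean, null | Inflation at ratio 0.5 | SE should be larger by |
|---|---|---|---|
| 0.5 | 1.19 | 1.13 | 6% |
| 1 | 1.39 | 1.26 | 12% |
| 2 | 1.78 | 1.52 | 23% |

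Multiplying 139.8 by 1.1295, 1.259 and 1.518 gives roughly 158, 176 and 212 infants per group.

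**4. Type I error of the stated model.** Simulated null trials, 8 cells × 35 infants, normal (z) limits. The ICU-period variance was set at about (0.01 − 0.005) / 0.3885 = 0.013 to match the protocol's correlations. The ranges cover several sets of runs (800 to 2000 trials per scenario), with durations fixed at 21 days or varying around that mean.

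| θ | REML-type | ML |
|---|---|---|
| 0 | 4.5–5.6% | 6.5–7.5% |
| 0.5 | 5.7–7.2% | 8.3–11.6% |
| 1 | 6.8–9.0% | 11.9–12.2% |
| 2 | 8.5–10% | 16–18.9% |

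The lowest values at θ = 0.5 come from runs with fixed durations. With an infant-level Pearson scale added, type I error is 4.6–5.7% (REML-type) and 6.0–9.6% (ML).

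**5. No true ICU-period variance.** Coverage of the nominal 95% interval at θ = 0.5, 1 and 2 is 0.955, 0.949 and 0.921 (REML-type), and 0.925, 0.903 and 0.885 (ML). A Poisson model with a Pearson scale gives 0.940, 0.952 and 0.958. The ICU × period variance was estimated at zero in 92–98% of ML fits. For REML-type fits, over all scenarios run, it was zero in 40–63%.

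**6. The opposite direction.** With t limits on 2 df (critical value 4.303), coverage is 0.998–1.000, and REML-type power at rate ratio 0.5 is about 4–5%. If one assumes that no new CRB is counted during the five days of antibiotic treatment named in Case 5 of the outcome definition, variance/mean is 0.86, 0.95 and 1.03 at θ = 0, 0.5 and 1. REML-type error is then 4.0%, 4.1% and 5.3%. If at most one CRB per infant is counted, it is 2–3%.

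**The case against.** The strongest reply is that the direction of the error is not settled by the documents. It depends on θ, on the estimator, on the df rule and on how repeat CRBs are counted, and none of these is given. Estimator and df rule are commonly left to the SAP, which is not shown, so their absence is no fault. With REML-type fitting and no true ICU-period variance, coverage is near nominal up to θ = 1. With limited recurrence, plain Poisson is neutral or conservative. All of this stands. A reader might infer that the interval is certainly too narrow; the documents support only that it can be.

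Three further inferences fail.

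- The ML figure of about 12% at θ = 1 is not all due to the distribution. ML already gives 6.5–7.5% at θ = 0 because there are few clusters, and a dispersion term does not remove that part.
- The manipulation contrast in the Background does not measure heterogeneity in risk. "This number of manipulations was significantly different between patients with and without CRB (70.7 vs 28.7" compares counts that also grow with time on the catheter, which the offset handles. The Discussion describes that population as preterm and term infants, whereas this trial enrols only 24+0 to 28+6 weeks.
- The sample size does not ignore clustering: it carries the ICU design effect. Only independence within an infant is assumed.

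What the reply does not remove is the stated choice itself. The protocol names the distribution and the single random term, and that combination leaves infant-level dispersion to a term with 2 df.

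**Conclusion.** The concern holds as a conditional one. The stated Poisson GLMM fixes the within-cell variance at the mean, and its only outlet for a departure is a variance on 2 df that is often estimated at zero. With repeat CRBs possible and risk said to vary with birth weight and gestational age, the interval can be too narrow. For assumed θ of 0.5 to 2 and an ICU-period variance of 0.013, type I error is about 7–10% with REML-type fitting and z limits, and about 10–19% with ML. The runs with fixed durations gave slightly less at θ = 0.5. Because CRBs per infant are few, the standard error needs to be only 6–12% larger for θ of 0.5 to 1 at rate ratio 0.5. The interval can be too wide instead if recurrence is effectively limited or 2-df t limits are applied. These results rest on the assumed θ and on infant-level rows. The 2 df and the reproduced sample size rest on the document alone.

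**What to change.** Keep the log link, offset, fixed effects and ICU × period random effect. Add an infant-level dispersion scale estimated from the roughly 272 within-cell df; it corrects for over- or underdispersion. A negative binomial GLMM is an alternative for overdispersion only, and it was not simulated here. State that the rows are infants, and pre-specify REML-type estimation and the denominator df rule together with the dispersion term, since each alters the interval. Apply the same to occlusions.

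The cost is a small change to the model code. Intervals are slightly wider if heterogeneity is present: about 2–3 points of power at θ = 1 (for example 61% against 64%). If heterogeneity is absent, essentially nothing is lost.

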## Methods/design

### Study design

The Multiline NEO study is a multicenter, cluster-randomized cross-over trial (Multiline NEO versus standard infusion system) over 28 months (Fig. 2). Four investigation centers (four clusters) will participate in the study and will be randomized into two groups to implement two different sequences. The randomization sequence will be performed using a computer-generated table provided by an independent statistician. The first group of two centers will apply the following sequence: Edelvaiss® Multiline NEO in the first period and standard infusion system in the second period. The second group of the other two centers will apply the inverse sequence: standard infusion system in the first period and Edelvaiss® Multiline NEO in the second. Each center will recruit the same number of subjects in period 1 and period 2, to obtain the same number of subjects per infusion system in each center.

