**Fig. 2 Fig2:**
[figure not shown]
Schedule of enrolment, interventions, and assessments

The infusion system (standard infusion system and Edelvaiss® Multiline NEO) that has been assigned randomly will be used until the removal of the CVC. If a CVC is changed during a multiline sequence, another multiline NEO and a standard infusion system will also be changed. The sequence will be changed after the last patient has been enrolled in the first sequence. The primary outcome is assessed from insertion of the CVC until its withdrawal. Contamination bias between the two periods is not expected as the conditions of use (connection and disconnection of infusion lines, flushing, decontamination of access ports, etc.) are similar for each group, except for two differences: 1) access to the infusion lines is outside the incubator with the Edelvaiss® Multiline NEO, whereas they are inside with the standard infusion line; and 2) the approved lifetime (CA marking) is 4 days for the standard infusion system and 21 days for the Multiline NEO.

Infants will be enrolled in the study at the time of placing a single-lumen CVC. The catheter is connected to either the Multiline NEO device or the standard infusion system. The single-lumen catheter is typically placed between the third and sixth day of life.

The trial was registered in ClinicalTrials.gov prior to recruitment, and trial reporting will be guided by the CONSORT Statement [15]. Protocol version 1, dated April 22, 2015, was approved by the Committee for the Protection of Persons (CPP) Nord Ouest IV (CPP no. 15/29) and French National Agency for Medicine and Health Product Safety (ANSM; ID-RCB number 2015-A00585–44). Modified protocol version 2, dated September 15, 2015, was approved by the CPP Nord Ouest IV on October 13, 2015 and ANSM on October 19, 2015. Modified protocol version 3, dated May 10, 2016, was approved by the CPP Nord Ouest IV on June 14, 2016.

Informed written consent is required from both parents for enrolment in the study.

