#### Secondary outcomes

The ID of occlusion will be analyzed by the same method as for the primary objective.The number of cases of septic shock and bronchopulmonary dysplasia will be analyzed using GLMM, taking into account the duration of stay in the ICU for each patient. The model will be identical to that used for the primary objective.The duration of oxygen therapy, of mechanical ventilation, and of parenteral nutrition will be analyzed using the linear mixed model. The ICU, the period, and the device will be considered as fixed effects and the ICU × interaction period as a random effect. In the case of non-normal model residuals, we will use a non-parametric test without taking the design into account (Mann-Whitney U test).

Cost data will be analyzed using Stata®. Depending on normality test results, mean costs will be compared across groups using Student’s *t*-test or non-parametric bootstrap. A GLM model and a Generalized Gamma model will be used with child characteristics at baseline as regressors and considering fixed effects for the device (standard infusion system or Edelvaiss® Multiline NEO) and the ICU. Cost-effectiveness will be established and ICER estimated, retaining the number of CRB incidents as health outcomes. The 95% confidence interval for ICER will be computed using Fieller’s method or the bootstrap method.

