## Discussion

It is essential to assess this new multi-lumen device specifically developed and designed for neonates so as to determine its effectiveness in preventing CRB in NICU patients.

Previous studies have reported the major impact of catheter manipulations on the occurrence of CRB in neonatology. In preterm and term newborn infants admitted to NICUs, the number of catheter manipulations was significantly different between patients contracting CRB or not (70.7 vs 28.7; *p* < 0.001) [6]. Moreover, CRB incidence increased significantly with decreased birth weight and gestational age. This study shows that specific manipulations (e.g., blood sampling through the central line and disconnection of the CVC) further increase the risk of CRB in neonates. Thus, the decrease in the number of infusion system manipulations will be correlated with a decrease in CRB [6].

Our hypothesis of a 50% reduction in CRB rates may not at first seem feasible but previous studies have shown an even more impressive decrease with strategies based on standardized nursing care, including bundles and checklists. As mentioned earlier, a recent study found a 77% reduction in CRB rates by implementing evidence-based measures for catheter care in an NICU [16].

The cluster-randomized crossover design of the study has several advantages. As the intervention is applied to all participants in a unit, contamination between interventions can be avoided and investigator cooperation is improved. As the interventions are applied (successively) in the same unit, a smaller number of units is required. The cluster-randomized crossover design ensures good team training in the handling of devices as their use is repeated during each period.

This trial has limitations. First, identification of CRB must be established on similar criteria. In the present study, it will be based on Neocat Network guidelines that differentiate between various types of bacteremia according to the number of cases of bacteremia and clinical or biological symptoms [20]. As special care must be taken to prevent contamination of blood culture during blood sampling, healthcare providers will have to be trained to comply strictly to the written procedure of evidence-based guidelines on blood culture sampling (Additional file 1).

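### The primary CRB model has no infant-level covariate, so a case-mix shift that follows the device within units would bias the device effect

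*Protocol article*

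**What the plan says.** **Allocation.** Under Study design: "Four investigation centers (four clusters) will participate in the study and will be randomized into two groups to implement two different sequences". Allocation is therefore by whole center. The same section says of entry "Infants will be enrolled in the study at the time of placing a single-lumen CVC", and of the switch "The sequence will be changed after the last patient has been enrolled in the first sequence". Consent is required from both parents, infant by infant. Study procedure leaves the date of catheter insertion to the care team.

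**Primary model.** Statistical analysis, Primary outcome, gives the model in full. It is a GLMM for the number of CRB incidents with log link, "a Poisson distribution, and the logarithm of catheter duration as the offset variable". On the fixed effects: "we will consider the device (standard infusion system or Edelvaiss® Multiline NEO), the period, and the ICU as fixed effects". The ICU-by-period interaction is the random effect. The secondary clinical outcomes use the same model or a linear mixed model with the same terms. The opening of the Statistical analysis section has baseline characteristics described by group and no more.

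**Prognosis.** The Discussion reports from a cited study that "CRB incidence increased significantly with decreased birth weight and gestational age". The inclusion criteria admit gestational ages from 24+0 to 28+6 weeks.

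**Costs.** The cost models, by contrast, are to be fitted "with child characteristics at baseline as regressors".

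**The concern.** In an individually randomised trial with concealed allocation, infant risk is balanced by design, and an unadjusted model is at worst inefficient. Here randomisation acts on four centers, and each infant is recruited after the center's device for the period is fixed. That staff know the device is an inference, but a fair one: no concealment is described, and Study design says that line access is outside the incubator with one device and inside it with the other. Who is approached, who consents and when the catheter is placed could then differ between a unit's two periods in a way that follows the device.

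If that happened, the difference in infant risk would be read as a device effect. It could run in either direction, producing a spurious benefit or hiding a real one. Gestational age and birth weight are the factors that the protocol itself links to CRB. An infant-level term would also take up part of the between-infant variation in rate that the Poisson model otherwise treats as absent.

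**Working it through.** **1. The plan's own figures reproduce.** Inputs from Sample size estimation: 18.5 and 9.25 per 1000 catheter-days (a 50% reduction), two-sided 5%, power 80%, 21 days per infant, ICC 0.01, inter-period correlation 0.005.

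- Chi-square formula without continuity correction: n = [1.960·√(2p̄q̄) + 0.842·√(p₁q₁ + p₂q₂)]² / (p₁ − p₂)², with p₁ = 0.0185, p₂ = 0.00925 and p̄ = 0.013875. This gives 2510 catheter-days per group, as stated.
- 2510 / 21 = 119.5, so 120 infants.
- Design effect with 35 per cell: 1 + 34 × 0.01 − 35 × 0.005 = 1.165 (stated as 1.16).
- 120 × 1.165 = 139.8, so 140 per group, 35 per ICU and period, 280 in total.

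The sample size is not in question. It supplies the standard error used below.

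**2. Standard error of the log rate ratio.** 140 × 21 = 2940 catheter-days per group, so 54.39 expected events at the control rate and 27.195 at half of it.

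- No effect: √(1.165 × 2 / 54.39) = 0.207.
- Rate ratio 0.50: √(1.165 × (1/54.39 + 1/27.195)) = 0.253. Wald power is Φ(0.693/0.253 − 1.96), about 78%.

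**3. Which case-mix shifts reach the device effect.** Write the mean gestational age in ICU i, period j as center level + period level + d × (device indicator) + chance cell deviation.

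- Center level: absorbed by the ICU fixed effects.
- Period level: absorbed by the period effect, because the two sequences run in opposite order.
- Chance cell deviation: carried into the standard error by the ICU-by-period random effect. There are 8 cells and 6 fixed parameters (intercept, device, period, 3 for ICU), leaving 2 cell-level degrees of freedom.
- d × device: has the same pattern as the device term, so no term in the stated model separates it from the device effect.

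**4. Size of the bias from d.** If the CRB rate is multiplied by k per additional week of gestation, a gap of d weeks between device groups multiplies the apparent rate ratio by k^d. Neither k nor d is in the document. I assume k = 0.80 to 0.90 and d = 0.25 to 0.5. Type I error is 1 − Φ(1.96 − b/0.207) + Φ(−1.96 − b/0.207), with b = −d·ln k. With the gap reversed and a true ratio of 0.50, power is Φ((0.693 − b)/0.253 − 1.96).

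| k, d (assumed) | Apparent ratio if truth is 1 | Type I error | Apparent ratio if truth is 0.50, gap reversed | Power |
|---|---|---|---|---|
| 0.90, 0.25 week | 0.974 | 5.2% | 0.513 | about 75% |
| 0.80, 0.5 week | 0.894 | 8.4% | 0.559 | about 63% |

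**5. How large a gap is by chance.** With gestational age uniform over five weeks (assumed), the SD is 5/√12 = 1.44 weeks. The standard error of a difference in means with 140 per group, ignoring clustering, is 1.44 × √(2/140) = 0.17 week. A gap of 0.25 week is about 1.5 standard errors, and 0.5 week is about 2.9.

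**The case against.** A design-based model without covariates is a legitimate primary analysis. The article condenses a longer protocol, and an adjusted analysis may sit in an analysis plan that is not shown. That is true, but the article states the primary model term by term. The point concerns that stated choice, and an unseen document does not alter it.

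Several stronger readings are tempting, and the document does not support them.

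- *Any case-mix drift between a unit's periods goes straight into the device effect.* It does not. Step 3 shows that common drift and stable center differences are removed, and chance cell differences go to the standard error. Only a shift that follows the device biases the estimate.
- *The protocol calls these strong predictors.* It reports a significant association from a cited study of preterm and term infants. It gives no gradient within 24+0 to 28+6 weeks.
- *Parents know the device when they consent.* Nothing says so. Only staff awareness can fairly be inferred.
- *Selection is shown.* Nothing in the text shows that device knowledge changes who is enrolled, and eligibility is worded alike for both devices.
- *The cost models contradict the primary model.* They serve a different aim with a different specification. They show only that some baseline child characteristics are meant to be used.

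The objection to the size also stands in part. Under the assumptions in step 5, a 0.25-week gap is ordinary chance already covered by the nominal error rate, and 0.5 week would need real selection. What remains is that the stated model has no defence against selection that follows the device.

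**Conclusion.** The point holds in limited form. The primary GLMM carries no infant-level covariate in a design where randomisation does not by itself protect infant balance within a unit, and where the protocol reports that CRB rises with lower birth weight and gestational age. A case-mix shift that follows the device would pass into the device rate ratio.

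Its size cannot be derived from the document. Under the assumed 10-20% change per week and 0.25-0.5 week gap, a true ratio of 1 would appear as 0.89-0.97, with type I error of about 5.2% to 8.4%. Larger distortions can be produced with larger inputs: 1.5-fold per week of lower gestation and a full week's gap give an apparent ratio of 0.67 and 50% type I error. Nothing in the text supports values that extreme. The case for change rests on the mechanism and the low cost, not on a demonstrated bias.

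**What to change.** Before database lock, prespecify gestational age (continuous), and birth weight or its z-score for gestation if recorded at baseline, as infant-level fixed covariates in the primary GLMM. Do the same in the matching models for the secondary clinical outcomes. Keep the model as now written as a named sensitivity analysis. It would also help to report screened, eligible and consented infants by ICU and period, so that selection can be judged.

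The cost is one line in the model statement. Gestational age is already an eligibility item. Collection of birth weight is not stated in the article and should be confirmed. Covariates that vary between infants do not use up the 2 cell-level degrees of freedom, and the total of 280 is unchanged. The article reports recruitment as ongoing, so on that status the change could still be made in advance; an adjustment added after an imbalance is seen would be post hoc. Adjustment corrects only measured imbalance, and selection on unrecorded features of the infant would remain.
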